# INTRODUCTION

This Statistical Analysis Plan (SAP) details the statistical and data related aspect of a planned manuscript on assessing whether rectus abominis muscle atrophy (*defined as a thinner muscle on the stoma side as seen on a postoperative computer tomography (CT) scan*) constitutes a protective factor for parastomal hernia (*defined as any herniation of intraabdominal content beyond the abdominal wall or a hernia sac identified in the prone or supine position on CT scan (if only the latter was available)*) as well as whether surgical technique used in colostomy construction constitutes a risk factor for rectus abdominis muscle atrophy and whether stoma placement (*measured from the medial limit of the muscle on 1-year CT scan)* constitutes a risk factor for parastomal hernia.

# ANALYSIS OBJECTIVES

The primary objective is to investigate if rectus abdominis muscle atrophy is a risk factor for development of parastomal hernia one year after surgery.

Secondary objectives are:

1. Are any of the investigated operative techniques risk factors for developing rectus abdominis muscle atrophy?
2. Is stoma placement measured from the medial limit of the rectus abdominis muscle a risk factor for developing parastomal hernia?

# STUDY METHODS

Data are drawn from the Stoma-Const study[[1](#_ENREF_1)], a prospective randomized study comparing the difference in risk for developing parastomal hernia one year after surgery with patients randomized to one of three surgical techniques:

- Cruciate incision (control)
- Circular incision
- Reinforcement of abdominal wall with a mesh around the stoma

The data material from StomaConst was deemed appropriate for use in a repeat retrospective analysis of rectus abdominis muscle atrophy and stoma placement in the rectus abdominis muscle.

# ANALYSIS POPULATION, TYPE OF ANALYSIS

## Analysis population

The analysis population consists of all patients who were included in the original study for whom a one-year CT examination was performed at all Swedish centres.

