## Type of analysis

The patients will be analyzed per protocol.

VARIABLES AND ENDPOINTS
Primary objective

The primary endpoint is the risk ratio between groups with and without rectus abdominis muscle atrophy for having parastomal hernia one year after surgery. The primary endpoint is derived from a modified Poisson regression model controlling for several covariates.

The variables associated with the primary objective are presence of rectus abdominis muscle atrophy <*varname_RAMatr>* and parastomal hernia at one year <*varname_Parastomal hernia>*.

Presence of rectus abdominis muscle atrophy will be determined by simultaneous retrospective examination by two radiologists of one-year CT examinations. Both assessors will examine the same image material, note their own judgment (rectus abdominis muscle atrophy yes/no) and then reach a consensus judgment. Cohen’s kappa will be reported as a measure of inter-rater agreement.

The determination of parastomal hernia at one year performed in the Stoma-Const trial will also be used in this study.

Further details are given in Table 1.

Secondary objectives

The secondary endpoints are the risk ratios between surgical techniques for developing RAM atrophy, and the risk ratio of a difference of stoma placement in RAM, measured from its medial limit, for developing parastomal hernia, respectively. The secondary endpoints are derived from modified Poisson regression models controlling for several covariates.

For the surgical techniques endpoint, the alternative technique of reinforcement of abdominal wall with a mesh around the stoma will be compared to the control techniques of cruciate incision and circular incision.

The variables associated with the secondary objectives are surgical technique <*varname_surgtec>* and presence of RAM atrophy <*varname_RAMatr>*, and stoma placement in RAM <*varname_stomaloc>* and parastomal hernia at one year <*varname_* parastomal hernia*>*, respectively.

Stoma placement in RAM will be determined by one radiologist assessor, measuring the distance from the medial RAM limit to the medial stoma border in mm.

Further details are given in Table 1.

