# HANDLING OF MISSING VALUES AND OTHER DATA CONVENTIONS

Missing values will be handled by listwise deletion in all analyses.

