### Interpretation of results

Due to randomization of surgical technique in the data material, any estimated effects of surgical technique on risk of rectus abdominis muscle atrophy can be interpreted causally.

Estimated effects of rectus abdominis muscle atrophy on risk of parastomal hernia and of stoma location on risk of rectus abdominis muscle atrophy cannot be interpreted causally. Instead, any such effects should be interpreted as correlational.

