## Sample size

The StomaConst study based its sample size on a power computation using a two-sided proportion test using normal approximation of the binomial distribution to obtain 80% power for a significance level of 0.05 and a true difference in proportion of 20%. This gave a sample size of 62 per group (three groups, one for each surgical technique).

For the present study, only patients for whom a one-year CT examination was performed at one of the Swedish centers are included, giving a sample size of 140. Approximating the incidence of rectus abdominis muscle atrophy as 37% for the mesh arm and 2% for the cruciate/circular arm (following Täckström 2022)[[2](#_ENREF_2)], 21 subjects are expected to display rectus abdominis muscle atrophy. Using the same test and significance level as above and assuming 44% incidence of parastomal hernia in the group without rectus abdominis muscle atrophy (following Correa Marinez 2020)[[1](#_ENREF_1)], this allows detection of a difference in proportion of 30% with 80% power for the primary endpoint.

For the secondary endpoint investigating risk ratio of surgical techniques for developing rectus abdominis muscle atrophy, the surgical technique arms consist of 88 subjects (cruciate/circular) and 52 subjects (mesh) respectively. Assuming rectus abdominis muscle atrophy incidence per arm as above, this gives >99.9% power.

Power for the secondary endpoint investigating risk ratio of stoma position for developing parastomal hernia is not easily computable in advance without knowledge of the distribution of stoma position in the sample. Thus, this power computation will be performed post-hoc.

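### The causal reading of the technique effect on atrophy rests on randomisation alone, but only patients with a one-year CT are analysed, so it needs a stated condition and a bounding analysis

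*SAP*

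**What the plan says.** The Analysis population section takes "all patients who were included in the original study for whom a one-year CT examination was performed at all Swedish centres". Atrophy can be known only for those patients, since it comes from "simultaneous retrospective examination by two radiologists of one-year CT examinations". The Type of analysis section adds "The patients will be analyzed per protocol", and the missing-data section adds "Missing values will be handled by listwise deletion in all analyses".

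On the ground that technique was randomised, the Interpretation of results section states without qualification that "any estimated effects of surgical technique on risk of rectus abdominis muscle atrophy can be interpreted causally". The same section limits the association of atrophy with hernia to a correlational reading.

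Under Sample size, "the surgical technique arms consist of 88 subjects (cruciate/circular) and 52 subjects (mesh) respectively". For the parent trial, "This gave a sample size of 62 per group (three groups, one for each surgical technique"). The number actually randomised at Swedish centres is not given, and neither is the number without a one-year CT in each arm.

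The list of planned tables and figures includes a flow chart and a demographics table of the whole trial beside the analysed subset. The Additional analyses section plans nothing, and the causal graph has no node for being scanned.

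**The concern.** Randomisation makes the arms comparable among those randomised, not among those who later have a scan. If having a one-year CT depends on arm and on something related to atrophy, the scanned mesh and scanned control patients differ for reasons other than technique. A causal reading therefore needs a further assumption, and the SAP leaves it unstated.

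This is separate from the per-protocol grouping: it would remain if every scanned patient were analysed in the arm assigned. It is also separate from the restriction to Swedish centres, which by itself would not break randomisation.

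What is at stake is mainly the size of the effect. Planned power for the technique comparison is already above 99.9%, so rejecting the null is hardly in doubt. The new information is the risk ratio, and its denominator rests on about two control events.

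**Working it through.** **Inputs (SAP, Sample size).** 88 cruciate/circular and 52 mesh patients; assumed atrophy 2% and 37%; two-sided 0.05; planned size 62 per technique.

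**The plan's own figures.** Expected cases: 52 × 0.37 + 88 × 0.02 = 19.24 + 1.76 = 21.0, as stated. Power for 2% against 37% by the normal approximation is 99.95%, in agreement with the stated figure of more than 99.9%.

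**Baseline risk ratio.** 0.37 / 0.02 = 18.5. In whole patients, (19/52) / (2/88) = 16.1, with a 95% interval of 3.9 to 66 on the log scale.

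**How many could be unseen.** The SAP does not say. The only available ceiling uses the planned size: 124 − 88 = 36 controls (29%) and 62 − 52 = 10 mesh patients (16%), together 46 of 186. This is an assumption. It takes planned for randomised numbers, and it mixes patients from outside Swedish centres with Swedish patients lacking a CT. The number of unseen controls, M, is therefore varied.

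**Illustration.** With k atrophies among M unseen controls and the mesh risk unchanged:

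RR = 0.37 / [(1.76 + k) / (88 + M)]; in whole patients, RR = (19/52) / [(2 + k) / (88 + M)].

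Half of the baseline is 9.25 and 8.04 respectively.

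| M | k | RR from 18.5 | RR from 16.1 | Atrophy rate among unseen controls at which RR halves |
|---|---|---|---|---|
| 10 | 3 | 7.6 | 7.2 | about 22–25% |
| 20 | 3 | 8.4 | 7.9 | about 13–15% |
| 36 | 3 | 9.6 | 9.1 | about 9–10% |
| 36 | 4 | 8.0 | 7.6 | about 9–10% |

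So 3 unseen control atrophies more than halve the ratio when M is 10 or 20, and 4 are needed when M is 36.

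The same point by rate, with M = 36: the control rate is (1.76 + 36q) / 124. For q = 5%, 10% and 20% it is 2.9%, 4.3% and 7.2%, and the risk ratio is 12.9, 8.6 and 5.1. At q = 2% it stays at 18.5.

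**Direction.** Suppose none of 10 excluded mesh patients and 3 of 36 excluded controls had atrophy. Then 19/62 against 5/124 gives RR 7.6 (95% interval 3.0 to 19.4; Fisher p about 1 in a million). Still with no excluded mesh patient affected, about 20 of the 36 controls would need atrophy before p exceeds 0.05 (p = 0.06 at 20).

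**Does the split show unequal loss?** 52 of 140 against an expected one third: binomial p = 0.37. It does not.

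**The case against.** The strongest reply is that the loss in question could be small. The 36 is not a count of Swedish controls without a CT, and a reader who sets 88/124 (71%) beside 52/62 (84%) might infer that scans were missed more often in the control arm. The documents do not support that. The denominators are planned sizes, centre exclusion is mixed in, and the observed split is compatible with equal loss. This stands.

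Second, halving the ratio needs unseen controls to have atrophy at about 9–10% or more, against the SAP's 2%, with the mesh risk left at 37%. No part of the SAP supports such a one-sided difference. This also stands, so the figures illustrate sensitivity and do not estimate bias.

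Third, the scenario values all lie inside the interval of 3.9 to 66, and fragility from two events would exist with complete follow-up. That is true of the imprecision, which the planned confidence interval will show. The interval does not cover bias from who was scanned, so it does not justify the unqualified causal sentence.

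Fourth, the models already adjust for age, BMI, sex, comorbidity and method of surgery. If missing scans depend only on arm and the model covariates, the adjusted analysis of scanned patients largely deals with them. This stands too, but it is a condition that the SAP should state, and it is not what the SAP gives as its reason.

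Finally, the flow chart and the demographics table will help a reader, but the SAP does not say that either is given by randomised arm, and neither qualifies the causal statement.

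**Conclusion.** The causal sentence is wrong as justified. Randomisation alone does not support it in a set defined by a later scan; comparability of unscanned Swedish patients across arms is also required. This conclusion does not depend on any of the numbers.

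The size of any bias cannot be determined from the SAP. Under assumed numbers of unseen controls (10 to 36) and an unchanged mesh risk, 3 to 4 unseen control atrophies would more than halve the risk ratio. Equal atrophy rates in seen and unseen controls would leave it as it is. The direction is very probably safe, so a reader should not infer that the mesh finding itself is in doubt.

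Nor should the point be carried over in full to the primary endpoint. The SAP already reads that association as correlational, so selection by scan is a limitation to state there, not a contradiction.

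**What to change.** 1. Keep the CT set as the main analysis set.
2. In Interpretation of results, make the causal statement conditional on missing one-year CTs being unrelated to atrophy, given arm and the model covariates.
3. In the planned Figure 1, give for each randomised arm the number randomised at Swedish centres and the reasons for having no one-year CT.
4. Pre-specify one bounding (tipping-point) analysis for the mesh comparison. Assign a range of atrophy rates, separately by randomised arm, to Swedish patients who were eligible for a one-year CT but lack one. Report patients who died before one year separately and do not assign them a status. The crude risk ratio is the practical scale, because stoma placement is itself read from the CT and is unknown for unscanned patients.
5. State selection by scan as a limitation of the primary endpoint.

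Inverse-probability weighting is optional. Its natural predictors other than centre (arm, age, sex, BMI, comorbidity, method of surgery) are already in the model, and weights from baseline data cannot correct for scans missed because of atrophy or stoma symptoms.

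The cost is a few lines of SAP text, patient counts by arm, one simple extra analysis and a more guarded causal claim.

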## Covariates, stratum and subgroups

Models for primary and secondary endpoints will be adjusted for potentially influential background variables by including as covariates the following variables:

1. Age

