2. BMI
3. Sex
4. Method of surgery (laparoscopic/open surgery)
5. Comorbidity as defined in the Stoma-Const trial including diabetes and cardiovascular disease. Defined as yes or no to one of several co-morbidity questions (question 15 in preoperative questionnaire)
6. Stoma aperture area (from the perioperative CRF question 16, fascia incision diameter
7. Stoma placement in the rectus abdominis muscle (where it is not the endpoint variable) measured by one radiologist as the distance from the midline to the beginning (medial) of the stoma aperture

These covariates will be investigated for potential multicollinearity before modelling. If serious multicollinearity is detected, some variables may be excluded.

Further details are given in Table 1.

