## Primary endpoint

The primary endpoint will be investigated using modified Poisson regression models using a sandwich estimator to compute confidence intervals and p-values, following Zou (2004), with parastomal hernia at one year as the response and MRA as a covariate. Other covariates to be adjusted for are stated in the “Covariates” section of the SAP. If clear overdispersion is detected in response data, it will instead be modelled using a negative binomial model.

The surgical technique variable will be included as a covariate in the model, as it is a potential confounder.

The result will be presented as a risk ratio for parastomal hernia at one year between MRA yes/no groups with 95% confidence interval and p-value for testing the null hypothesis of no difference in risk.

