## Secondary endpoints

The secondary endpoints will be investigated using modified Poisson regression models using a sandwich estimator to compute confidence intervals and p-values[[3](#_ENREF_3)]. For the secondary endpoints concerning surgical techniques, MRA at one year will be included as the response and surgical technique as covariates. For the secondary endpoint concerning stoma placement, parastomal hernia at one year will be included as the response and stoma placement will be included as a covariate. Other covariates to be adjusted for are stated in the “Covariates” section of the SAP. If clear overdispersion is detected in response data, it will instead be modelled using a negative binomial model.

For the secondary endpoint concerning stoma placement, the surgical technique variable will be included as a covariate in the model, as it is a potential confounder.

The results for the endpoints concerning surgical technique will be presented as risk ratios for MRA between surgical technique groups with 95% confidence intervals and p-values for testing the null hypotheses of no difference in risk.

The results for the endpoints concerning stoma placement will be presented as risk ratios for parastomal hernia at one year for a unit difference in stoma placement with 95% confidence interval and p-value for testing the null hypothesis of no difference in risk.

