### Dagitty code

dag {

bb="-4.843,-4.178,3.772,4.524"

"Mesh/No mesh" [pos="-0.125,-3.452"]

"Open/laparoscopy" [pos="-2.478,-2.181"]

"Rectus abdominis muscle atrophy" [exposure,pos="0.586,-0.093"]

"Stoma aperture" [pos="-4.125,0.439"]

"Stoma placement in the rectus abdominis muscle" [pos="-1.144,2.404"]

"parastomal hernia" [outcome,pos="-0.605,-0.502"]

Age [pos="2.074,-2.559"]

BMI [pos="1.634,2.119"]

Comorbidity [pos="3.054,0.088"]

Sex [pos="0.853,3.799"]

"Mesh/No mesh" -> "Rectus abdominis muscle atrophy"

"Mesh/No mesh" -> "parastomal hernia"

"Open/laparoscopy" -> "Rectus abdominis muscle atrophy"

"Open/laparoscopy" -> "parastomal hernia"

"Rectus abdominis muscle atrophy" -> "parastomal hernia"

"Stoma aperture" -> "parastomal hernia"

"Stoma placement in the rectus abdominis muscle" -> "Rectus abdominis muscle atrophy"

"Stoma placement in the rectus abdominis muscle" -> "parastomal hernia"

Age -> "Rectus abdominis muscle atrophy"

Age -> "parastomal hernia"

BMI -> "Stoma placement in the rectus abdominis muscle"

BMI -> "parastomal hernia"

BMI -> Comorbidity

Comorbidity -> "Rectus abdominis muscle atrophy"

Comorbidity -> "parastomal hernia"

Sex -> "Rectus abdominis muscle atrophy"

}

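### Centre is in neither the covariate list nor the DAG, so it may confound the stoma placement–hernia risk ratio in these pooled multicentre data

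*SAP*

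**What the plan says.** The SAP's Analysis population section takes trial patients "for whom a one-year CT examination was performed at all Swedish centres". Its Sample size section repeats that "only patients for whom a one-year CT examination was performed at one of the Swedish centers are included", which gives 140 patients. The number of centres is not stated.

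On adjustment, the section on covariates, stratum and subgroups says "Models for primary and secondary endpoints will be adjusted for potentially influential background variables by including as covariates the following variables". It then lists age, BMI, sex, open or laparoscopic surgery, comorbidity, stoma aperture area and stoma placement. Despite its heading, that section names no stratum. The endpoint sections add one variable. For the primary model, "The surgical technique variable will be included as a covariate in the model, as it is a potential confounder". For the placement model, "For the secondary endpoint concerning stoma placement, the surgical technique variable will be included as a covariate in the model".

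The Dagitty code has ten nodes and none is centre. BMI is the only cause drawn for stoma placement, and open/laparoscopy has no cause at all. No reason is given for leaving centre out.

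**The concern.** The trial randomised the construction technique, not where in the rectus muscle the stoma was placed. Placement is decided at surgery, so operator and centre habit are natural candidate causes. Centres may also differ in hernia risk, or in how readily a hernia is seen on CT. If both hold after the listed covariates, a centre that places stomas more laterally and records more hernias will produce a placement–hernia association that is only a difference between centres.

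The plan will report that association as an adjusted risk ratio with a confidence interval and p-value, in answer to whether placement is a risk factor. The SAP draws a DAG and fixes an adjustment set, so the omission of centre lies within what this document decides.

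**Working it through.** **The plan's own figures.** None concerns centre. Those used as inputs reproduce.

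- Expected atrophy: 0.37 × 52 + 0.02 × 88 = 19.24 + 1.76 = 21.0 (stated 21).
- Primary power, 44% of 119 against 14% of 21, pooled normal approximation: pooled proportion (2.94 + 52.36)/140 = 0.395; null SE √(0.395 × 0.605 × (1/21 + 1/119)) = 0.1157; alternative SE √(0.14 × 0.86/21 + 0.44 × 0.56/119) = 0.0883. Then (0.30 − 1.96 × 0.1157)/0.0883 = 0.83, so power is 79.6% (stated 80%).

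**Placement and hernia.** From the SAP: n = 140, and 44% hernia (given there for patients without atrophy, used here as the average). Assumed: two centres of 70, placement with SD 1 within centre and means d apart, hernia risks Δ apart, no true placement effect, no other covariates. Between-centre differences alone give a covariance of dΔ/4 and a placement variance of 1 + d²/4. To first order:

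- log RR per SD ≈ (dΔ/4) / [(1 + d²/4) × 0.44]
- SE ≈ √[(0.56/0.44) / (140 × (1 + d²/4))]

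| d (SD) | Hernia rates | log RR | RR | SE | Ratio to SE | False rejection, formula | Simulated RR; false rejection |
|---|---|---|---|---|---|---|---|
| 0.5 | 39% / 49% | 0.0125/(1.0625 × 0.44) = 0.027 | 1.03 | 0.093 | 0.29 | 6% | 1.03; 7% |
| 0.8 | 34% / 54% | 0.04/(1.16 × 0.44) = 0.078 | 1.08 | 0.089 | 0.89 | 14% | 1.08–1.09; 14–15% |
| 0.8 | 29% / 59% | 0.06/(1.16 × 0.44) = 0.118 | 1.12 | 0.089 | 1.33 | 26% | 1.13; 28–29% |

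The simulations fit robust Poisson models to at least 1000 trials per setting, so Monte Carlo error is about 1 point. With centre in the model, the RR is 1.00–1.01 and false rejection 4–6%.

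If d = 0 or Δ = 0 the numerator is zero and the RR is 1.00. In simulation, false rejection was then 5.6–5.8%.

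**Atrophy and hernia.** Placement is a covariate in this model, so a route from centre through placement to atrophy is closed. Centre matters only if it reaches atrophy another way. Suppose it does, with atrophy rates e₁, e₂ and hernia rates r₁, r₂ in two equal centres:

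RR = [(e₁r₁ + e₂r₂)/(e₁ + e₂)] / {[(1 − e₁)r₁ + (1 − e₂)r₂]/(2 − e₁ − e₂)}

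- Atrophy 10%/20%, hernia 39%/49%: 0.4567/0.4371 = 1.045.
- Atrophy 5%/25%, hernia 34%/54%: 0.5067/0.4282 = 1.18.

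Both settings average 15% atrophy, which matches 21/140.

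**Cost of the centre term.** With two assumed centres, the SE of the placement log RR rose in simulation from about 0.095 to 0.100, that is 0.100/0.095 ≈ 1.05, or about 5%.

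**The case against.** The strongest reply is that the SAP contains no evidence of confounding, and that the two-centre set-up aligns the differences by construction. Both points stand. With six equal centres (also an assumption), a similar spread, and placement and hernia differences drawn independently, the mean RR was 1.00. False rejection was 6.7–8.0% without centre and 5.7–6.7% with it. The upper end of the range above is therefore an unfavourable case. A single dataset could still be aligned by chance.

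Some differences between centres are already absorbed. Open/laparoscopic surgery, aperture area and technique are covariates. One radiologist measures placement and two agree on atrophy, so local readers do not set the exposures. Operator habit is the main route that remains.

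The SAP's Interpretation of results section limits the atrophy–hernia result to a correlational reading. It seems to intend the same for stoma location, although it names atrophy as the outcome there. This softens the consequence but does not remove a distorted risk ratio or p-value.

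Three stronger readings are tempting, and the document supports none of them:

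- *Centre does confound these comparisons.* No centre counts or centre-level rates are given, so only "may" can be defended.
- *The same path undermines the primary endpoint.* The covariate list includes "Stoma placement in the rectus abdominis muscle (where it is not the endpoint variable", and this closes that path.
- *Adjusting for a randomised technique but not for centre is inconsistent.* The DAG has mesh causing both atrophy and hernia. Technique can therefore confound atrophy–hernia even though it was randomised, and adjusting for it there is right.

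**Conclusion.** The gap is real: the data are multicentre, the adjustment set and DAG omit centre, and no reason is given. It bears mainly on the secondary placement–hernia endpoint, where the exposure was not randomised and the DAG gives it BMI as its only cause.

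The size cannot be known from the SAP. Under the two-centre assumption, a null RR moves to about 1.03–1.13 per SD with 6–29% false rejection. The bias is nil when centres differ in only one of placement and hernia risk, and the effect is small when their differences are mild or unaligned. For the primary endpoint, centre is a matter for sensitivity analysis. The change is worth making because it is cheap and has to be fixed before the data are analysed.

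**What to change.** - Add centre to the DAG as a possible cause of stoma placement, open/laparoscopy and hernia, and of atrophy if that is judged plausible.
- Include centre as a fixed effect in the placement–hernia model. Set the rule for combining low-volume centres, with its threshold, in advance. Pooling unlike centres leaves some confounding, so the rule should combine as few as possible.
- Report the primary atrophy–hernia model with and without centre as a sensitivity analysis. With about 21 atrophy cases expected and eight adjustment variables already planned (the seven listed plus technique), many centre indicators could be costly there.
- Say which centre is meant. The population is defined by where the CT was performed, and the centre that built the stoma is the one relevant to placement.

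The cost is SAP wording, one degree of freedom per extra centre and a slightly wider interval: about 5% in the SE for placement with two centres, and more if there are many. Centre should be on record, since belonging to a Swedish centre defines the population, but this should be confirmed for the operating centre.
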